# Efficacy and safety of Dingkun pill for female infertility patients with low prognosis undergoing in vitro fertilization-embryo transfer: study protocol for a multicenter, double-blind, randomized, placebo-controlled trial

**DOI:** 10.1186/s13063-020-04502-z

**Published:** 2020-06-19

**Keywords:** Traditional Chinese medicine, Dingkun pill, In vitro fertilization, Diminished ovarian reserves, Poor ovarian response

## Abstract

**Background:**

Approximately 15% of couples in the reproductive age are affected by infertility. Women with diminished ovarian reserves (DOR) or with a poor ovarian response (POR) are required to undergo in vitro fertilization and embryo transfer (IVF-ET) to achieve pregnancy. However, studies indicate that poor response to gonadotropin stimulation has been reported in women undergoing IVF-ET. Results from two recent clinical studies in China suggest that traditional Chinese medicine (TCM) formula Dingkun pill (DKP) showed a curative effect by improving the clinical pregnancy rate in women with DOR and POR. However, the heterogeneity of the studies does not allow one to draw a definitive conclusion on the therapeutic effect of DKP. Therefore, the purpose of this study was to investigate the effect of DKP on improving the clinical outcome of pregnancy of IVF-ET in women with low prognosis.

**Methods:**

A multicenter, double-blinded, randomized placebo-controlled trial was conducted. A total of 460 infertile patients undergoing IVF or intracytoplasmic sperm injection (ICSI) were recruited from 12 public hospitals in China. Participants were randomly divided into the experimental group (DKP formula) or the placebo group (control) at a ratio of 1:1. All patients were treated with GnRH antagonist protocol and ovarian stimulation performed for 5 weeks (from the 5th day of the previous menstrual cycle to the day of oocyte retrieval). The patients were followed up for 6 months to record their conception outcome. The primary outcome is to compare the pregnancy outcome to those under placebo treatment. Secondary outcomes included the total count of the retrieved oocyte, embryo quality, endometrial thickness on ET day, implantation rate, and early miscarriage rate.

**Discussion:**

Currently, no multicenter, double-blind, randomized, placebo-controlled trials have been performed on the use of the DKP formula to improve on the clinical outcome of the conception of IVF-ET in women with low prognosis. DKP might provide a good clinical solution for females with low prognosis and undergoing IVF. There is no contemporary Western medicine to improve on the clinical outcome of conception in IVF-ET in women with low prognosis. Therefore, it is important to undertake a well-designed randomized trial to determine the effect of DKP in improving the clinical outcome of the conception of IVF-ET in women with low prognosis.

**Trial registration:**

Chinese Clinical Trial Registry (ChiCTR). Trial registration number: ChiCTR1900026614. Registered on 16 October 2019.

## Background and rationale

Infertility affects approximately 15% of couples of reproductive ages and female infertility is a global reproductive health problem [1]. Currently, postponing childbearing due to socio-economic reasons has shown an increasing trend worldwide. The consequences of this are an increased number of women having a poor ovarian response (POR) prior to IVF due to their old age. Women in their mid to late thirties are reported to more likely have diminished ovarian reserves (DOR) due to irreversible intrinsic aging of the ovaries, and this highlights the need to focus on this group of women undergoing IVF-ET [2, 3]. Even though IVF-ET has become an effective and widely available treatment for infertile couples, women with DOR or POR to exogenous gonadotropin stimulation present a challenge to reproductive experts [4].

Low prognosis is one of the most intractable problems of IVF-ET treatment, occurring in approximately 47% of women with DOR, and 55% of these women aged ≥ 35 years [5–7]. Patients with low prognosis require not only an increased dose of gonadotropin (Gn) but also increased time for ovarian stimulation during an IVF cycle. However, there are a number of associated disadvantages such as fewer oocyte yield, poorer embryo quality, and pregnancy outcome [8]. These factors cause emotional, physical, and financial burden and distress for the couple, especially when multiple treatment cycles are required [9]. Regardless of the various pre-treatment strategies available including coenzyme Q10 [10] and dehydroepiandrosterone (DHEA) [11], there is a lack of sufficient evidence on the ability of these therapeutic agents to reverse low prognosis especially in women of advanced age and with DOR [12].

DKP is one of the traditional Chinese medicines first used during the reign of Emperor Qianlong of the Qing dynasty (A.D. 1636–1912) as a “holy medicine in the emperor’s harem”, and it was used exclusively by the imperial court. DKP components include ginseng, deer antler, safflower, *Caulis spatholobi*, *Radix rehmannia preparata*, *Angelica*, *Scutellaria*, *Rhizoma cyperi*, *Leonurus japonicus houtt*, ligustrazine, *Rhizoma corydalis*, and other 30 traditional precious Chinese herbs. It is commonly used in the treatment of several medical conditions such as irregular menstruation, dysmenorrhea, osteopyrexia and fever, leukorrhea with reddish discharge, and metrostaxis. DKP is used to tonify the liver and kidney, invigorating qi and nourishing blood, regulating menstruation, relaxation to combat depression, promoting blood circulation, and relieving pain. In Chinese medicine practice, TCM pathogenesis in elderly women with low prognosis is mainly manifested by spleen and kidney deficiency, blood deficiency, and liver depression, which is consistent with the TCM syndrome type of DKP. DKP is reported in previous studies to have a curative effect on increasing the clinical factors affecting pregnancy rate in women with DOR and POR [13, 14]. However, the heterogeneity of these studies does not provide definitive conclusions about the therapeutic effects of DKP, mainly due to the use of small sample size, unknown randomization methods, inconsistent inclusion criteria, and lack of a placebo group. Therefore, it is important to carefully design a randomized controlled trial to confirm the efficacy of DKP pills in improving the clinical outcome of the conception of IVF-ET in women with low prognosis.

## Methods

### Objective

The objective of our present study will be to investigate the effect of DKP pills on improving the clinical outcome of IVF-ET in women with low prognosis.

### Trial design and setting

This is a prospective, multi-center, randomized, double-blinded, placebo-controlled, superiority study. Eligible participants will be randomly assigned to the experimental group (DKP) or the control group with a 1:1 ratio. The participants will be recruited from 12 hospitals across mainland China. The study flow chart and schedule are shown in Fig. 1 and Table 1 (SPIRIT Figure), respectively.

**Fig. 1 Fig1:**
[figure not shown]
The study flowchart

**Table 1 Tab1:** Schedule of the study process (SPIRIT Figure)

	Study period				
	Enrollment	Allocation	Post allocation		
Timepoint*	1st visit	0 week	1–6 weeks	7–12 weeks	4–6 months
**Enrollment:**					
Eligibility screen	**√**				
Informed consent	**√**				
Allocation by TCM team		**√**			
**Interventions:**					
DKP treatment			**√**		
Placebo treatment			**√**		
**Assessments:**					
Basic ovarian reserve test (AFC, bFSH, AMH, etc.)			**√**		
Laboratory index measurement (oocyte, zygote, embryo, etc.)				**√**	
Pelvic ultrasound evaluation (endometrium thickness and classification)				**√**	
IVF pregnancy outcome					**√**
Liver and renal function assessment				**√**	**√**

The main study site and coordinator are the Reproductive and Genetic Center of Integrated Traditional and Western Medicine and the Affiliated Hospital of Shandong University of TCM, respectively. The study is performed in collaboration with the Shandong University of TCM. The project team leader and main project coordinator have regularly communication and study visits have been performed at all study sites. In addition, meetings with all study sites are held annually or more frequently.

### Eligibility criteria

#### Inclusion criteria

Participants ≥ 35 years with poor pre-stimulation ovarian reserve parameters (AFC < 5, AMH < 1.2 ng/mL) and with an expected poor ovarian response (fewer than four oocytes) after standard ovarian stimulation will be recruited in this study.

#### Exclusion criteria

Patients will be excluded if their age ≥ 45 years, BMI ≥ 30 kg/m^2^, karyotyping abnormalities in both partners, endometriosis, hydrosalpinx, congenital or acquired dysplasia of the uterus, and other contraindications requiring assisted reproductive technology.

### Interventions

#### TCM DKP formula preparations

In traditional Chinese medicine, the decoction is prepared by boiling in water for hours. However, DKP (Lot No. Z20059003, Shanxi Guangyuyuan Medicine Co., Ltd., China) preparation will adopt the water-honeyed pill protocol according to the Chinese Pharmacopoeia (ChP) 2015 Edition standard [15] and ChP 2005 Edition. The “DKP water-honeyed pill” standard [16] is approved by the China Food and Drug Administration (CFDA). Each TCM bottle is filled with 7 g DKP.

The genuine medicinal materials are used in all kinds of traditional Chinese herbs, and the specific purchasing locations are stipulated as township-level sales points where genuine medicinal materials are located, which are purchased in the same batch. The medicinal materials are processed in strict accordance with the requirements, and standard operation procedures are formulated. The test results of drug quality were consistent with the Chinese Medicine Standards of the State Food and Drug Administration.

#### Placebo preparation

The placebo will be provided by Shanxi Guangyuyuan Medicine Co. Ltd. (China). The DKP placebo will be a mixture of 55% starch and 45% caramel mixed, dried, crushed, and lumped together. The daily doses of the placebo are packed in individual TCM bottles for easy consumption under the ChP 2015 Edition standard the Good Manufacture Practice of Medical Products (GMP) standard. Patients in the placebo group will consume the same amount of placebo as the treatment group.

The placebo and the herbal medicines used to make DKP are identical in appearance, color, smell, taste, packaging, usage, and dosage [17]. During the production of placebo, the selection of condiments, colorants, and other excipients should be carefully carried out, and strictly in accordance with the Chinese Medicine Standards of the State Food and Drug Administration.

#### Study process

Prior to the control of ovarian hyper-stimulation (COH), all participants will receive DKP 7 g twice daily on the 5th day of their menstrual cycle until the oocyte retrieval day.

##### COH

GnRH antagonist (cetrorelix; Merck Serono, Darmstadt, Germany) is administered subcutaneously at a daily dose of 0.25 mg when there is at least one follicle measuring ≥ 12 mm in mean diameter on the trigger day, with 150–450 IU/day of recombinant FSH (Puregon, MSD, Courbevoie, France; Gonal-F, Merck-Serono, Lyon, France) and urinary FSH (hMG, Menotrophin for Injection, Livzon Pharmaceutical Group Inc., Guangdong, China). Gonadotropin doses will be determined based on individual patient’s characteristics. Final oocyte maturation will be triggered when more than two ovarian dominant follicles measuring ≥ 18 mm are visible by ultrasound. Final oocyte maturation will be achieved using either a single 0.2 mg injection of GnRH agonist (Triptoreline, Decapeptyl, Ipsen, France) or 250 μg of recombinant hCG (rhCG, Ovitrelle, Serono, France). Oocyte retrieval will be performed after 35–36 h by transvaginal ultrasound-guided aspiration.

##### Oocyte retrieval and embryo culture

BD Falcon IVF medium (Becton, Dickinson and Company, Franklin Lakes, NJ, USA) will be used to collect the Oocytes and perform embryo culture. Incubation conditions will be set at 6% CO_2_, 5% O_2_, and 37.0 °C (C200 CO_2_ Incubator, Labotect Labor-Technik-Göttingen GmbH, Göttingen, Germany). Culture oocytes will be inseminated for IVF or decumulated for ICSI.

Transfer of two high-quality embryos will be performed on day 3, and the surplus frozen on day 3 or day 5 based on the routine at different sites. All good quality embryos will be cryopreserved via vitrification (CBS-ViT-HS, CryoBioSystem®, L’Aigle, France). Dimethylsulfoxide and ethylene glycol will be used as cryoprotectants (Irvine Scientific Freeze Kit®, Irvine Scientific, Newtown Mount Kennedy, Ireland, and Vitrification Kit 101, Cryotech®, Tokyo, Japan).

##### Endometrial preparation and embryo transfer

Artificial endometrial preparation will consist of sequential administration of E_2_ valerate and injectable progesterone. A total of 2 mg E_2_ valerate will be administered twice daily for 14–16 days, and the dose later adjusted based on the endometrial thickness measured by vaginal ultrasonography. For endometrial thickness ≥ 7 mm, injectable progesterone supplementation will be initiated while for endometrial thickness < 7 mm, the patients will continue taking oral E_2_ until the endometrium attains the required threshold. About 20 mg of progesterone will be administered and FET will be performed after 3 days. Ultrasound-guided soft catheter embryo transfers will be performed.

#### Adherence

Each study center will have a local coordinator responsible for a case report form (CRF) to ensure adequate recording of individual participant’s data. To improve data validity, several methods will be used to assess drug compliance, including TCM bottle count and weekly telephone follow-up. Unused medicines will be counted and recorded.

#### Concomitant care

All participants will not be allowed to take other Chinese herbal supplements or nutritional supplements to enhance ovarian reactivity for 3 months prior to their enrollment into the study, since they may affect the effectiveness of the DKP formula.

### Outcome measurements

#### Primary outcomes

The primary outcome is the ongoing clinical pregnancy rate, defined as the presence of intrauterine gestation sac with fetal heart rate at 7 weeks of gestation.

#### Secondary outcomes

Secondary outcomes include total retrieved oocyte count, embryo quality, endometrial thickness on ET day, implantation rate, early miscarriage rate, and safety assessment on the TCM formula. Early miscarriage is defined as the spontaneous loss of pregnancy within the first 13 weeks of gestation. Implantation rate is defined as the number of gestational sacs per the number of embryos transferred.

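### In frozen transfers, transfer-day endometrial thickness is read at least 17 days after DKP stops and after estradiol was steered by that same thickness, so a DKP effect can be masked (minor)

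*Protocol article*

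**What the plan says.** The Secondary outcomes section reads "Secondary outcomes include total retrieved oocyte count, embryo quality, endometrial thickness on ET day, implantation rate" and continues with further items. It does not say whether the transfer day is that of a fresh or a frozen transfer.

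The sections that bear on this reading are:

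- **End of treatment (Study process).** Study medication is taken "until the oocyte retrieval day". The Abstract gives the same end point and a dosing period of 5 weeks.
- **Fresh route (Oocyte retrieval and embryo culture).** "Transfer of two high-quality embryos will be performed on day 3, and the surplus frozen on day 3 or day 5".
- **Frozen route (Endometrial preparation and embryo transfer).** Estradiol valerate is given for 14–16 days, with "the dose later adjusted based on the endometrial thickness measured by vaginal ultrasonography". Progesterone starts once the lining is at least 7 mm; below that, "the patients will continue taking oral E_2_ until the endometrium attains the required threshold". After progesterone, "FET will be performed after 3 days".
- **Scan before retrieval (COH).** "Final oocyte maturation will be triggered when more than two ovarian dominant follicles" of at least 18 mm are seen on ultrasound. Then "Oocyte retrieval will be performed after 35–36 h". The section uses this scan for follicles only.
- **Schedule (Table 1).** Study medication is in the column for weeks 1–6. The pelvic ultrasound for endometrial thickness is in the column for weeks 7–12.

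**The concern.** In a woman with a frozen transfer, two things stand between DKP and the transfer-day reading. The first is time: she has been off DKP for weeks. The second is the preparation regimen. Thickness there is the variable on which the estradiol dose is adjusted, and it is also the gate that must be passed before progesterone starts. A woman with a thin lining gets more estradiol, or longer estradiol, until she reaches 7 mm. The outcome is thus read after treatment has been used to bring it to a target.

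If DKP thickens the endometrium, the preparation can close part of the gap between the arms before anyone measures it. A small or null difference would then be hard to interpret: DKP may have no endometrial effect, or the effect may have faded or been evened out. Readings from fresh transfers carry neither problem to the same degree, yet they fall under the same outcome name.

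**Working it through.** **Plan's own figure.** The plan gives no effect size or power for endometrial thickness, so there is nothing to reproduce for this outcome. Its primary-outcome sample size (25% v 40%, two-sided 0.05, 90% power, pooled Z test) reproduces at 203 per group. It is used below only as the group size.

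**Step 1: time since the last dose.** Retrieval, when DKP stops, is day 0.

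- Fresh day-3 transfer: 3 days.
- Frozen transfer, shortest: 14 days of estradiol + 3 days of progesterone = 17 days.
- Frozen transfer at the upper end of the stated estradiol range: 16 + 3 = 19 days, and longer if the lining is still below 7 mm.
- Frozen transfer after a failed fresh transfer, assuming 14–28 days between that transfer and the start of estradiol: 3 + 14 + 14 + 3 = 34 days to 3 + 28 + 16 + 3 = 50 days.

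The document does not state when estradiol starts. The 17 days assumes that it starts no earlier than retrieval; a later start only lengthens the interval.

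**Step 2: the scan that times the trigger.** It takes place at least 35–36 hours before retrieval, while DKP is still being taken and before any preparatory estradiol. A reading there has neither the lag nor the steering.

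**Step 3: place in Table 1.** With 5 weeks of dosing, retrieval is at day 35.

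- Trigger scan: shortly before day 35, in the column for weeks 1–6.
- Fresh transfer: day 35 + 3 = 38, week 38/7 = 5.4.
- Earliest frozen transfer: day 35 + 17 = 52, week 52/7 = 7.4.

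The scheduled ultrasound (weeks 7–12) therefore fits a frozen transfer better than a fresh one. The oocyte and embryo row has the same window, however, so the table is coarse and does not settle which transfer is meant.

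**Step 4: illustration of the 7 mm floor only.** Every mean, SD, gain and frozen share here is an assumption. Let thickness without the rule be X ~ N(μ, σ) on placebo, with mean μ + 0.6 mm on DKP and 203 women per arm. A share φ of readings (frozen) follows max(X, 7) and the rest follow X. With a = (7 − μ)/σ, standard normal distribution function Φ and density f:

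E[max(X, 7)] = 7Φ(a) + μ(1 − Φ(a)) + σf(a)

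For μ = 7.5, σ = 2 and φ = 1, placebo gives 8.073 and DKP (μ = 8.1) gives 8.466, a visible gain of 0.393 mm.

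| Placebo mean, SD (mm) | Visible gain at φ = 0.1 / 0.5 / 1.0 (mm) | Power lost (points) |
|---|---|---|
| 7.5, 2 | 0.579 / 0.496 / 0.393 | 0.9 / 4.2 / 6.5 |
| 8, 2 | 0.584 / 0.522 / 0.445 | 0.5 / about 2.5 / 4.1 |
| 8.5, 1.8 | 0.590 / 0.552 / 0.504 | 0.2 / 0.9 / 1.5 |
| 10, 2 | 0.597 / 0.585 / 0.570 | 0.0 / 0.2 / 0.4 |

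Without the floor, power is 85.6% for SD 2 and 91.9% for SD 1.8.

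The model has clear limits. It puts the floor on the transfer day, whereas the plan applies it at progesterone start, about 3 days earlier. It leaves out the estradiol dose adjustment. It also carries the full 0.6 mm into frozen cycles, as if nothing faded after DKP stopped. It therefore illustrates one mechanism and does not estimate the total.

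**The case against.** The best defence is that thickness on the day of transfer is a sensible outcome in its own right. It describes the conditions under which the embryo is placed, and the plan never calls it a measure of DKP's action while the drug is being taken. The same preparation rule applies in both arms. Few women may be affected: Inclusion criteria expects fewer than four oocytes and two embryos go to the fresh transfer, so surplus embryos should be uncommon. A trigger-day reading has its own faults: it is not at transfer, and women cancelled before the trigger have none.

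Most of this stands. It is why transfer-day thickness should be kept and the added reading placed beside it. It does not remove the difficulty that, in frozen cycles, a lack of difference says little about what DKP did to the endometrium.

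Three stronger readings are tempting and not supported:

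- **That the comparison is biased.** The rule is the same in both arms and favours neither.
- **That frozen readings necessarily understate a DKP effect.** The lag and the dose adjustment have no known size here, and the floor model covers neither. The documents support only that an effect can be masked.
- **That the primary outcome is left undefined.** Primary outcomes does not name the transfer that counts. It does fix the event; Data analysis fixes the intention-to-treat comparison and the Abstract the 6 months of follow-up. A condensed article may leave the counted transfer to the full protocol. Counting later frozen transfers could move power either way, depending on assumed success rates. Naming the transfer there, and for the implantation rate, would be a wording clarification at most.

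**Conclusion.** The point holds as a minor one about a secondary outcome. In frozen transfers, transfer-day thickness is read at least 17 days off DKP, on a variable that the preparation itself steers, and it is pooled by name with fresh readings taken about 3 days off DKP. The 17 days rests on the stated durations and on estradiol starting no earlier than retrieval.

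The size cannot be fixed, because the share of frozen transfers is not given. Under the assumed floor model the loss is negligible when one reading in ten is frozen (at most 0.9 points of power). It is modest when all are (0.4–6.5 points, with 66–95% of the assumed gain still visible). The sample size and the primary analysis are unaffected.

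**What to change.** 1. In COH and Secondary outcomes, add endometrial thickness at the ultrasound that times the trigger, in all women who reach it, as the measure of DKP's effect on the endometrium.
2. Keep transfer-day thickness as an outcome and report it separately for fresh and frozen transfers.
3. Change the endometrial ultrasound entry in Table 1, now at weeks 7–12, so that it also covers the trigger scan and matches the transfer days.

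The cost is protocol wording, one extra thickness reading at a scan already done, and one case report form field for fresh or frozen. The downside is that the added measure does not describe the endometrium at transfer and is missing for women cancelled before the trigger. The choice between fresh and frozen transfer stays with the sponsor.

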#### Randomization and allocation concealment

Patients will be randomly divided into two groups (1:1 ratio) using computer-generated random numbers managed by the Integrative Medicine team. CARDS identifying the DKP group and the placebo group will be placed in sealed, opaque envelopes and distributed by designated professional managers. Both medications (DKP formula and placebo) will be prepared in a manner that they will appear similar in appearance, flavor, and smell. Blinding of the clinicians, patients, and outcome and data analysts will be done. To ensure high accuracy, the trial will follow the updated guidelines from the Consolidated Standards of Reporting Trials (CONSORT) 2010 Statement [18] and the SPIRIT-TCM Extension 2018 for reporting of parallel-group randomized clinical trials [19]. Un-blinding will only occur in exceptional circumstances when matters cannot be resolved with ongoing randomization, and this will be performed by an authorized investigator. All un-blinding events will be reported and their reasons are given on the corresponding CRF.

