#### Data analysis

Statistical analyses will be performed using SPSS software version 26.0 (IBM Corp, Armonk, NY). Kolmogorov-Smirnov test will be used to test the normality of the data. Normally distributed continuous variables are reported as mean ± SD, while non-normally distributed continuous variables are reported as median and IQR. Categorical variables are reported as absolute and relative percentage frequencies. For comparison of the baseline characteristics and outcomes, independent Student’s *t* test or the Mann-Whitney *U* test are used to evaluate the mean or median differences between the placebo and DKP groups for normally distributed continuous variables, and the Pearson *χ*^2^ test for categorical variables.

Multiple imputation will be used to process missing values in the data of this study. The intention-to-treat analysis is used to examine the differences in the clinical pregnancy rate for the two treatment arms in the primary analysis using the Pearson *χ*^2^ test. Similarly, the multivariate regression model is used to adjust the results based on potential confounding factors. All the tests are two-tailed, and the significance level is set as *p* < 0.05.

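### Implantation rate is counted per embryo, but women are randomised and the only test named for proportions assumes independent units, so its p-value and interval would be too optimistic

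*Protocol article*

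**What the plan says.** All references are to the protocol article.

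- **Outcome.** Under Secondary outcomes, "Implantation rate is defined as the number of gestational sacs per the number of embryos transferred". The denominator is embryos, not women.
- **Embryos per transfer.** Under Oocyte retrieval and embryo culture, "Transfer of two high-quality embryos will be performed on day 3".
- **Expected yield.** The inclusion criteria select women "with an expected poor ovarian response (fewer than four oocytes) after standard ovarian stimulation".
- **Unit of randomisation.** Under Randomization and allocation concealment, "Patients will be randomly divided into two groups (1:1 ratio) using computer-generated random numbers".
- **Test.** The Data analysis section sets its methods out "For comparison of the baseline characteristics and outcomes": t test or Mann-Whitney for continuous variables, "and the Pearson *χ*^2^ test for categorical variables". It adds that "the multivariate regression model is used to adjust the results based on potential confounding factors". Neither the test nor the model is said to allow for embryos that share a woman.

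**The concern.** Embryos placed in one woman share the oocyte source, the uterus and the stimulation cycle, so their chances of implanting tend to move together. A chi-square test on the table of embryos by implanted or not counts each embryo as a separate piece of evidence. With positive correlation, two embryos from one woman carry less information than two from different women. The test then claims more precision than the trial has.

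Implantation rate is one of the secondary results that would be read as support for an effect of the pill. A falsely small p-value there could lend weight to the primary result, or be quoted alone if the primary result is not significant. This is not a detail left to a fuller document: the article names both the outcome unit and the test, and the two do not fit together.

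**Working it through.** **The plan's own figure.** The only calculation in the article is the primary sample size (rates 0.40 and 0.25, two-sided 5%, 90% power, pooled variance):

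n = [1.960 × √(2 × 0.325 × 0.675) + 1.282 × √(0.40 × 0.60 + 0.25 × 0.75)]² / 0.15² = (1.298 + 0.838)² / 0.0225 ≈ 202.8, so 203 per arm.

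This matches the stated 203. It is counted in women and does not depend on implantation. The article states no figure for implantation, so what follows measures the size of the problem and does not check a stated value.

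**Inputs for implantation**
- Embryos per woman: m = 2 from the planned transfer, taking one transfer per woman.
- Nominal two-sided α = 0.05 (Data analysis section).
- Intraclass correlation (ICC) between embryos of one woman: not in the documents. Assumed range 0.1 to 0.5.

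**Formulas**
- Two embryos for every woman: design effect DE = 1 + (m − 1) × ICC = 1 + ICC.
- Half the women with one embryo and half with two: weighting by embryos, DE = [1 + 2 × (1 + ICC)] / 3 = 1 + 2 × ICC / 3.
- True type I error = 2 × [1 − Φ(1.96 / √DE)].
- Shortfall in the standard error = 1 − 1/√DE.

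| Assumed ICC | DE, all two | SE too small by | True α, all two | DE, half one | True α, half one |
|---|---|---|---|---|---|
| 0 | 1.00 | 0% | 0.050 | 1.000 | 0.050 |
| 0.1 | 1.10 | 4.7% | 0.062 | 1.067 | 0.058 |
| 0.2 | 1.20 | 8.7% | 0.074 | 1.133 | 0.066 |
| 0.3 | 1.30 | 12.3% | 0.086 | 1.200 | 0.074 |
| 0.5 | 1.50 | 18.4% | 0.110 | 1.333 | 0.090 |

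**Worked line.** At ICC 0.2 with two embryos each: 1.96 / √1.2 = 1.789, and 2 × [1 − Φ(1.789)] = 0.074.

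**Check by simulation.** Beta-binomial outcomes were simulated with 230 women per arm, an assumed implantation probability of 0.15 in both arms and 40,000 repetitions. For ICC 0.1, 0.2, 0.3 and 0.5, the rejection rates were 0.064, 0.072, 0.086 and 0.110 with two embryos each. With half the women on one embryo they were 0.057, 0.066, 0.072 and 0.090. The formula holds.

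**The case against.** **The article does not say that chi-square will be run on pooled embryos.** It assigns chi-square to categorical variables in general. A rate computed for each woman and compared by t test or Mann-Whitney would keep the woman as the unit. That reading cannot be excluded, so the finding is conditional. But the outcome is defined as sacs over embryos, and the natural reading of such a proportion under this plan is chi-square. Nothing in the text guards against it.

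**The effect may be small.** The ICC is assumed, and with fewer than four oocytes expected, many women may have one embryo or none. Both points stand. At ICC 0.1 the error is about 6% on either embryo assumption, and one-embryo transfers lower it throughout. The same fact has a second consequence: women without a transfer leave the implantation denominator altogether, so the comparison no longer covers everyone randomised.

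**Stronger readings that the document does not support.** A reader might infer that the implantation rate itself is mis-stated. It is not: clustering leaves the pooled proportion unchanged and affects only its precision. A reader might also infer that miscarriage is compared only among women who conceived, a group formed after randomisation. The article says only that "Early miscarriage is defined as the spontaneous loss of pregnancy within the first 13 weeks of gestation". It gives no denominator and no such restriction. A condensed article can leave the denominator to the full protocol or analysis plan, so its absence is not held against the plan here.

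**Conclusion.** The point holds for implantation. As written, the plan pairs a per-embryo outcome with a test that assumes independent units, in a trial that randomises women. If the test is applied to embryos, the type I error of a nominal 5% comparison is about 6% to 11% with two embryos per woman, and about 6% to 9% if half the women have one. This rests on an assumed ICC of 0.1 to 0.5 and one transfer per woman. At ICC 0 there is no error.

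The issue is confined to the precision of one secondary outcome. The primary outcome is counted per woman, and its sample size reproduces. No finding is made on how miscarriage is compared. The remedy is cheap and clearly better than the named test, so the change should be made.

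**What to change.** **Implantation.** State in the Data analysis section that implantation is compared between arms with the woman as cluster, by GEE or a cluster-robust variance, instead of Pearson chi-square on embryos. Report also gestational sacs per woman randomised, with women who had no transfer counted as zero, so that one version of the result keeps everyone randomised.

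**Cost.** Analysis wording only, with no new data. Relative to the naive interval, the width grows by √DE − 1: with two embryos each, about 5% at ICC 0.1, 10% at 0.2 and 22% at 0.5.

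**Optional, if a comparison that takes losses into account is wanted.** Count women with a fetal heart rate at 7 weeks, subtract only those whose loss came after that scan and up to 13 weeks, and divide by women randomised. Subtracting all early miscarriages from the primary outcome would be wrong, because losses before the 7-week scan never entered the primary count. This version needs the date of each loss. Miscarriage per pregnancy can stay as a descriptive figure.
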